The treatable trait success story of chronic asthma certainly makes a case for the reappraisal of our approach to acute asthma.^6 7 43^ Is it time for precision medicine to attack the problem of asthma attacks? A worthwhile question, considering that corticosteroid toxicities appear after the lifetime equivalent of only four bursts (≥1000 mg cumulative dose) of prednisone—that is, four severe asthma attacks^44^—and the increasing levels of resistance to antibiotics observed, mainly due to inadequate prescriptions.^7 29^ Biomarker-guided management could avoid harm to individual patients and society stemming from the inappropriate use of OCs and/or antibiotics due to overuse or without proper consideration of their potential risks and side effects.^44 45^ Simply stated, corticosteroid and antibiotic stewardship can and should be assisted by acute POC testing.

Based on previous knowledge from chronic stable asthma and reports that asthma attacks are heterogeneous events, we hypothesise that treatment responses to OCs in acute asthma vary according to the underlying inflammatory phenotype. Specifically, we speculate that events identified by raised BEC and/or FeNO benefit most from OCs and that events presenting with low type 2 biomarkers have a lesser objective clinical and biological anti-inflammatory response but perhaps higher rates of airway infection or dysfunction. If this proves to be the case, we will be in a solid position to move forward with a randomised clinical trial comparing biomarker-directed OC use with the current ‘one-size-fits-all’ approach. An important secondary hypothesis of our study is that POC inflammatory and microbiological assessments in acute asthma are possible, acceptable and reliable. The ramifications of such findings would be to plan a clinical trial assessing biomarker-guided asthma attack management in primary care.

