### Participants

People ≥12 years old with physician-diagnosed asthma since >6 months experiencing an asthma attack as defined by GINA (episode characterised by a progressive increase in symptoms of shortness of breath, cough, wheezing or chest tightness that represent a change from the patient’s usual status)^2^ with a patient and/or physician decision to initiate a burst of OCs (but not yet started) will be assessed within 24 hours on weekdays after a screening telephone call. Exclusion criteria are a SARS-CoV-2-positive event, asthma treated with a monoclonal antibody or maintenance OCs, current smoking, significant overlapping cardiopulmonary disease (including chronic obstructive pulmonary disease, defined as age >40 years old AND persistent airflow limitation with forced expiratory volume in 1 s (FEV_1_)/forced vital capacity <0.7 AND >10 pack-year smoking history or α-1-antitrypsin deficiency), a confounding immunological state, ongoing pregnancy or contraindication to corticosteroids.

Although we will assess asthmatics with a history of physician-diagnosed asthma, patients included in the primary analysis and counting toward the target sample size will need to have objective proof of asthma as defined by international guidelines^2^ either based on the medical record or with a clinically required follow-up test ordered by the study respirologist and performed after study participation. Unconfirmed asthmatics data will be reported but not used for the primary analysis.

Non-atopic, non-smoking healthy volunteers with normal spirometry and no history of lung disease will form the control cohort. All participants (±their parent or legal tutor) must provide informed consent for the study protocol. Patients who cannot or refuse to participate in the diary card data collection for the home monitoring period will still be able to participate in all other study procedures.

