### Sample size

For our primary analysis, assuming a two-sided α error of 0.05, a T2:non-T2 event ratio of 1:1 and a mean±SD population difference in δ FEV_1_ of 10±10%, n=46 will provide 90% of power to detect the difference in our primary outcome on an unpaired two-sample t-test. According to a recent Canadian study that assessed the proportion of randomly selected adults with physician-diagnosed asthma who fulfil objective criteria to confirm the diagnosis of asthma, 18.3% of participants reporting a severe asthma attack in the past year (11 of 60) did not have asthma confirmed.^61^ We thus conservatively estimate that 20% of patients recruited will not count towards the n=50 needed for the primary analysis.

Including a cohort of 12 healthy control participants, each assessed during a single visit, is intended to enhance our ability to relativise demographics, lung function and inflammatory measurements observed in the study. Recruitment will continue until the target number of confirmed asthmatics and healthy controls has completed the study.

We acknowledge that the secondary and exploratory analyses will likely be underpowered and view these as exploratory but feasible within the proposed timeline of a pilot study serving to plan further clinical trials. Any significant finding for secondary and exploratory outcomes will require further confirmatory studies to support them.^62^

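### For patients without record proof of asthma, entry to the primary analysis is settled by a discretionary test after type 2 status and FEV1 change are known, and no all-enrolled comparison is stated

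*Protocol article*

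**What the plan says.** Under Participants, the protocol article admits people with physician-diagnosed asthma but restricts the primary analysis, and the count toward the target, to those with objective proof by international guidelines. There are two routes to proof: the medical record, or a "clinically required follow-up test ordered by the study respirologist and performed after study participation". For the rest, "Unconfirmed asthmatics data will be reported but not used for the primary analysis".

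Under Primary outcome, type 2 status is fixed from visit 1 blood eosinophils and FeNO, and the outcome is the change in FEV1 between visits. Under Statistical analyses, those are visits 1 and 2, that is, day 0 and day 7. Table 1 has a doctor reviewing test results at day 7.

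Under Sample size, 20% of recruits are expected not to count, and "Recruitment will continue until the target number of confirmed asthmatics and healthy controls has completed the study". The sensitivity analyses named under Exploratory outcomes and Statistical analyses concern sex, gender, race and diversity. None concerns confirmation status.

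**The concern.** A patient without record proof joins the primary set only if a later test is ordered, done and positive. All three steps follow the exposure and the outcome, and the person ordering the test belongs to the study team. The article states no masking of that decision. Because the proof must be objective, it may well correlate with the outcome, which is itself a lung-function change. Type 2-high and type 2-low patients may also differ in how often they already have proof on record.

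If both links exist, selection works unequally in the two groups and the primary difference shifts. Recruitment runs to a number of confirmed patients, so those who drop out of the count are replaced by others who pass. The result is meant to feed the power calculation for a randomised trial, so a shifted difference would carry over into that trial's size.

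**Working it through.** **1. The plan's own sample size.** Inputs, all from Sample size: "assuming a two-sided α error of 0.05", "a T2:non-T2 event ratio of 1:1", "population difference in δ FEV_1_ of 10±10" (per cent, so standardised difference 10/10 = 1.0), and "n=46 will provide 90% of power to detect the difference in our primary outcome on an unpaired two-sample t-test". The noncentral t calculation needs 22.02 per group, rounded up to 23, so 46 in total (power 91.2%; 22 per group gives 89.97%). The stated figure reproduces and is not in dispute. At 25 per group, power is 93.4%.

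**2. How many are removed.** Recruits needed for 50 confirmed: 50/(1 − 0.20) = 62.5, so 63. Removed: 63 − 50 = 13. The 20% rounds up the cited 11/60 = 18.3%.

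**3. Order of events.** Type 2 status, day 0. FEV1 change complete, day 7. Confirmation test, after participation. Whether participation ends at day 7 or at the day 97 contact, the test comes after both.

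**4. Simulated selection.** From the document: SD 10 and 20% unconfirmed. Assumed: 60% type 2-high and the record-proof rates, since the document does not give the share needing the later test. FEV1 change is drawn from N(5 + δ·T2, 10²). A patient is confirmed if proof is on record (probability by type 2 group) or if the later test passes, with logit(pass) = a + b·z. Here z is the standardised FEV1 change and a is set so that 20% overall are unconfirmed. Reruns agree within about 0.2 points.

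| Record proof, high / low | Slope b | Estimate, true δ = 10 | Estimate, true δ = 0 |
|---|---|---|---|
| 70% / 40% | 1 | 8.9 | −1.0 |
| 80% / 20% | 1 | 7.8 | −2.1 |
| 80% / 20% | 2 | 6.5 | −3.1 |
| 60% / 60% or 70% / 70% | 1 | 9.9 to 10.1 | about 0 |
| 70% / 60% | 1 | 9.8 | −0.3 |
| 40% / 70% | 1 | 10.7 | +1.0 |
| 70% / 40% | −1 | 10.8 | +1.0 |
| any | 0 | 10.0 | 0 |

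Share needing the later test at 80%/20%: 0.6 × 0.2 + 0.4 × 0.8 = 44%.

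**5. A second model.** Here the groups are 1:1, the same share of each group needs the test (25% to 60%), and 20% are removed. Log-odds slopes are 0.7 to 1.4.
- Confirmation depends on type 2 status only: 10.0, no bias.
- On FEV1 change only: 9.2 to 10.3 for a true 10, and 0 for a true 0.
- On both, additively: 8.1 to 10.6 for a true 10, and −1.4 to +0.5 for a true 0.
- On FEV1 change in opposite directions in the two groups: 10.6 to 13.4 for a true 10. For a true 0 the estimate is +0.7 to +3.5 and the test rejects in 6% to 25% of trials. This is the one case where equal need for the test does not protect.

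**6. Scale.** The standard error of the difference with 25 per group is 10 × √(2/25) = 2.8 points. The shift of 10 − 8.9 = 1.1 is under half of that; the shift of 10 − 6.5 = 3.5 exceeds it.

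**The case against.** **The target is confirmed asthma.** Removing people who do not have asthma defines that population and is not bias against it. This stands. Bias for that target arises only if true asthmatics fail the test, or are never tested, in a way related to FEV1 change. The simulations measure departure from the all-enrolled difference, so they mix a change of population with selection error. A reader might infer that the exclusion itself is the fault; the document does not support that.

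**The large shifts need strong joint assumptions.** This also stands. The 80%/20% case leaves only one in five type 2-low patients with proof on record. The Discussion expects most recruits from specialised asthma clinics, where earlier objective testing is plausible.

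**Discretion is already limited.** The guideline definition and the requirement of clinical need narrow it. They do not remove it, because ordering and completing the test still follow the outcome. The article names only the record or a post-study test as proof, so there is no ground for inferring that the study's own FEV1 change would be accepted.

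**Details of this kind often sit in a full protocol or analysis plan.** That is fair for the added analyses. The membership rule, however, is stated here, and the point rests on the rule. A promise to report unconfirmed patients' data is not a commitment to the type 2 comparison in everyone enrolled.

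**Primary care.** The Introduction's aim to "plan a clinical trial assessing biomarker-guided asthma attack management in primary care" follows the point-of-care hypothesis and does not set the population for the FEV1 comparison. It makes an all-enrolled estimate useful, but does not oblige the study to make it primary.

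**Conclusion.** The point holds for patients without record proof, whose share the article does not state. For them, membership of the primary set is decided after type 2 status and FEV1 change are known, by a test with discretion in its ordering. The primary difference can then be biased if confirmation is related to FEV1 change and the need for the test differs by type 2 status, or if the relation itself differs between the groups.

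Size and direction are unknown. With confirmation rising with FEV1 change in both groups, the assumed record rates in the first model gave 6.5 to 10.7 for a true 10. Similar record rates gave 9.8 to 10.1, and no link to FEV1 change gave 10.0. Dependence on type 2 status alone gives no bias. A reader might infer that the primary result is biased, or biased toward no difference, or that the whole set is affected. None of these follows: patients proven by record are untouched, and reversed rates reverse the sign. In a pilot observational study this is an inexpensive improvement to the plan and does not invalidate it.

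**What to change.** Keep the confirmed set as primary and pre-specify three additions.

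1. Repeat the primary comparison in all enrolled physician-diagnosed patients with both visits, and in those confirmed by record alone. Report both beside the primary result. The first involves no selection on confirmation; the second involves none made after the outcome.
2. Tabulate by type 2 group the numbers confirmed by record, confirmed by later test, test-negative and untested.
3. State that the confirmation decision applies the same guideline criteria to every patient without record proof, and is made without reference to visit 1 eosinophils, FeNO or the visit 1 to 2 FEV1 change, where existing staff allow.

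Items 1 and 2 cost a few sentences and extra runs on data already collected. Item 3 may be hard with a small team, hence the qualification. The downside is two or three estimates to present. The all-enrolled estimate describes a broader population that includes some people without asthma. The record-only set is smaller and less precise: at 70%/40%, 63 × 0.6 × 0.7 ≈ 26 and 63 × 0.4 × 0.4 ≈ 10 patients, with standard error 10 × √(1/26 + 1/10) ≈ 3.7 points.

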### Study visits

Visit 1 will be on day 0 of the asthma attack, with oral prednisone issued by the community pharmacy (40 mg×7 days) (figure 1). Concomitant antibiotic use will only be considered for patients with ≥1 of the following criteria: CRP >20 mg/L, procalcitonin >0.25 µg/L (when available), or positive sputum culture and/or multiplex POC test for a significant bacterial pathogen. Healthy controls will attend only visit 1. Multimodal assessments performed at study visits lasting ~2 hours are detailed in table 1. In visit 1, these comprise:

Medical history and examination, including vital signs, inhaler technique and adherence check (using prescription refills of community pharmacy), five-item Asthma Control Questionnaire (ACQ-5),^46 47^ dyspnoea rated on the modified Medical Research Council Scale,^48^ Visual Analogue Scale for respiratory symptoms, Pittsburgh Vocal Cord Dysfunction Index,^49^ Nijmegen Questionnaire,^50^ Hospital Anxiety and Depression Scale,^51^ chest X-ray.FeNO measurement (NIOX VERO, Circassia) and pre/post-bronchodilator oscillometry (Tremoflo C-100, Thorasys Thoracic Medical Systems) and spirometry plus peak expiratory flow.Peripheral blood tests (complete blood count with differential, serum CRP, total and specific serum IgE, biobank), POC-BEC (Sight OLO, Sight Diagnostics), urine sample (creatinine, biobank), nasosorption with nasal epithelial lining fluid (NELF), nasal swab for the ultrarapid ID NOW (Abbott Industries) SARS-CoV-2 molecular test, nasopharyngeal swab for rapid multiplex PCR using the BIOFIRE Respiratory 2.1 (RP2.1) Panel (bioMérieux). If no spontaneous sputum is available, following negative COVID-19 testing and post-bronchodilator FEV_1_ > 60% predicted value or >1.5 L, induced sputum collection with hypersaline nebulisation would then be performed, as done in a previous asthma attack study.^37^

**Table 1 T1:** Study visit overview

Visit	Screening	0	1–6	7	97
Location	Telephone	Clinic	Home	Clinic	Virtual±telephone
Consent	Given	Signature			
Inclusion/exclusion criteria overview	x	x			
SARS-CoV-2 test (ID NOW)		x		x	
Medical history		x		x	x
Physical examination by doctor		x			
Inhaler technique check		x			
Adherence check (call to community pharmacy)		x			
Check if patient picked up prednisone tablets			x		
Review of test results by doctor				x	±
Questionnaires					
Medical Research Council dyspnoea scale		x		x	
Asthma Control Questionnaire (5 items)		x	x	x	x
Visual Analogue Scale of asthma symptoms (6 items)		x		x	
Pittsburgh Vocal Cord Dysfunction Index		x		x	
Nijmegen Questionnaire		x		x	
Hospital Anxiety and Depression Scale		x		x	
Survey of % of home tests monitored				x	
Satisfaction questionnaire about point-of-care biomarker measurements: participant				x	
Satisfaction questionnaire about point-of-care biomarker measurements: letter and email sent to treating doctor				x	
Respiratory physiology					
FeNO measurement (NIOX)		x		X	
Teaching of FeNO measurement		x			
FeNO measurement		x	x	x	
Teaching of peak expiratory flow measurement		x			
DEP measurement		x	x	x	
Capillary blood eosinophils: sight OLO measurement		x		x	
Force spirometry—pre-bronchodilator		x		x	
Forced oscillation—pre-bronchodilator					
Salbutamol 400 µg		x		x	
Force spirometry—post-bronchodilator		x		x	
Forced oscillation—post-bronchodilator					
Inflammometry					
Hospital viral multiplex PCR (BIOFIRE on nasopharyngeal swab)		x		x	
Nasosorption		x		x	
Nasal cytology brushes		x		x	
Induced or spontaneous sputum collection for differential cell count+supernatant, plugs and cell pellet for biobank		x		x	
Induced or spontaneous sputum collection for hospital microbiology analysis		x		x	
Hospital blood tests (1 EDTA tube, 1 heparin tube): complete blood count with differential, C reactive protein		x		x	
Allergy testing (hospital blood tests; 1 tube) for total serum IgE, specific serum IgE: grass mix, weed mix, tree mix, mould mix, house dust mites *Dermatophagoides pteronyssinus* and *D. farinae*, *Aspergillus fumigatus*		x			
Research laboratory blood tests: 1 EDTA, 4 heparin, 2 serum, 1 whole blood for research laboratory (biobank)		x		x	
Chest X-ray		x			
Urine sample; urine creatinine for hospital; sample frozen for research laboratory (biobank)		x		x	

FeNO, fractional exhaled nitric oxide.

Visit 2 will additionally include a survey of adverse events relating to corticosteroids, patient satisfaction questionnaires and permission to contact the patient’s primary care provider for a physician survey about POC testing.

Visit 3 is a web-based survey reviewing the number of subsequent exacerbations, medication changes and ACQ-5 score and allowing the patient to prompt a call from the study team (or vice-versa if the study team has a test to follow up on).

All study visits will occur in the morning to avoid the confounding effect of circadian variation of type 2 inflammatory biomarkers.^51–53^

### Home monitoring

Between visits 1 and 2, patients will be invited to complete daily symptom scores, FeNO and peak expiratory flow measurements via a paper diary card.

### Follow-up visit

Ninety days after visit 2, patients will be contacted by email to complete an internet form containing ACQ-5, peak flow measurement and questions about asthma management.

### Data and sample management

Individual participant data will be collected prospectively and managed using REDCap electronic data capture tools hosted at the Université de Sherbrooke.^54 55^ Frozen samples will be anonymised and logged prospectively in a freezer map.

### Specimen processing and analysis

Due to multimodal biobanking (figure 2), the study is closely associated with—but not dependent on—the local Quebec Respiratory Health Research Network biobank (www.biobanque.ca). Nasosorption strips will be spun with NELF eluted from a plastic mesh and then frozen (−80°C).^56^ Sputum will be mixed with Dulbecco’s phosphate-buffered saline (DPBS) and supernatant frozen before differential cell counting, as previously described.^57^ Whole blood will be processed into serum, buffy coat, primary blood mononuclear cell isolates, and whole blood samples and preserved frozen. Nasal swabs will be analysed immediately using the ultrarapid ID NOW molecular test to rule out SARS-CoV-2. One nasopharyngeal swab on visit 1 will be analysed using a POC multiplex PCR for 22 respiratory viruses and bacteria (BIOFIRE RP2.1 Panel) to identify infectious contributors to the attack, while the other nasopharyngeal brushes plus sputum plugs will be RNA stabilised then frozen (2× in RNA-Protect and 1× flash frozen). If sufficient sputum is produced at visit 1, a sputum plug will be sent for conventional bacterial culture, and up to three other plugs will be frozen (1× with dithiothreitol-DTT, 1× dry, 1× in 10% glycerol). Urine samples will be frozen.

**Figure 2 F2:**
[figure not shown]
Multimodal and multicompartment sampling (biobanking) of highly phenotyped patients experiencing an asthma attack. In addition to many samples being analysed within the hospital laboratory, samples will be *biobanked within the Quebec Respiratory Health Research Network (QRHRN) biobank infrastructure (www.biobanque.ca). The collaborative nature of the biobank will allow further analyses and collaboration among QRHRN-affiliated academic research centres. Brackets indicate analyses not currently funded. CBC, complete blood count; CRP, C reactive protein; ddPCR, droplet digital PCR; MSD, Meso Scale Discovery; NAAT, nucleic acid amplification test; NP, nasopharyngeal; PBMC, peripheral blood mononuclear cell; PBS, phosphate-buffered saline; PRISMA, Phenotyping the Responses to Systemic Corticosteroids in the Management of Asthma Attacks; RAST, radioallergosorbent test; RP2.1, Respiratory 2.1.

At the end of the study, patient NELF, sputum DPBS-eluted supernatant, serum and urine will be thawed for inflammatory protein level measurements performed by multiplex electrochemiluminescent assays (Meso Scale Discovery, Meso Scale Diagnostics: Eotaxin-3, interferon-γ, IL-4/5/13/33, TARC, TSLP, tumour necrosis factor) and ELISA (sputum supernatant and urine cysteinyl leukotrienes corrected for creatinine). DNA and RNA will be extracted from nasopharyngeal brushes and sputum plugs. Quantitative digital droplet PCR, 16S ribosomal amplicon sequencing and shotgun metagenomics analysis will be used to detect and identify bacteria present in the samples. The 16S amplicon and shotgun metagenomics libraries will be sequenced using an Illumina Nextseq500 sequencer (Illumina).

### Outcome measures

#### Primary outcome

Change in the FEV_1_ between visits, with particular emphasis on a comparison based on the presence or absence of type 2 inflammatory events within the patient cohort. Specifically, we will classify type 2 high events on the basis of visit 1 BEC ≥0.15×10^9^ cells/L and/or FeNO ≥25 ppb.

#### Secondary outcomes

Change in ACQ-5 between visits according to type 2 inflammatory status.The proportion of patients who achieve a minimal clinically important difference (MCID) ≥10% for FEV_1_ and ≥0.5 points for ACQ-5, according to the presence of type 2 high or type 2 low events.^58^ The magnitude of response will be rated as poor, moderate or good if the change is <1×, ≥1× or ≥2× the MCID values, respectively.

#### Exploratory outcomes

The continuous association between baseline biomarkers (BEC and FeNO) and changes in symptom scores, sputum inflammometry, additional lung physiology parameters (impulse oscillometry), inflammatory mediators (type 2 cytokines, chemokines, alarmins, eosinophils) and microbiome diversity across different immune compartments (nasal epithelium, induced sputum, serum, urine).Comparative agreement and reliability of gold-standard BEC (hospital laboratory) versus POC test (Sight OLO).An appraisal of POC biomarkers using patient satisfaction scores and primary care physician surveys.A sensitivity analysis on all of the above assessing how sex at birth, gender (self-identified: female, male, other specify) and race (self-identified)^59^ influence treatment responses.

